# SCHEMA

**A Phase IV Randomized, Open Label Controlled Trial of Time-Limited Highly Active Antiretroviral Therapy (TL-HAART) in Patients with Acute or Early HIV Infection**

DESIGN: Within the context of a three-year phase IV randomized clinical trial, we will compare two different strategies for intervention following the diagnosis of acute or early HIV infection. Specifically, we will examine, in a randomized fashion, whether a one-year course of HAART provides lasting benefit in patients who have recently become infected with HIV. The principal study endpoint will be a comparison of the plasma viral load 24 months after initial presentation in treated vs. untreated patients. Additional endpoints will be the evolution of CD4 lymphocyte counts, safety and tolerability of antiretrovirals, and the need to initiate/re-initiate HAART over a 36 month time period following initial presentation. We will further examine whether the benefit is limited to a subset of such individuals, based on the presumed interval between exposure to HIV and initiation of therapy (acute vs. early). Staging of disease will be done in accordance with the AIEDRP staging algorithm (APPENDIX V) The highlights of the experimental design will be: 1) to attempt to include all patients meeting the NIH-approved definition of acute or early HIV disease (AIED, i.e., patients known to have been infected within the past 12 months), with emphasis on the recruitment of patients identified prior to the development of a complete anti-HIV antibody response ("pre-seroconversion"); 2) to allow for the individualization of the treatment regimen, with a special provision for patients carrying drug-resistant isolates; and 3) to administer HAART for a pre-determined length of time (i.e., one year) and then discontinue therapy. Taken as a whole, this approach will allow us to offer the opportunity to the vast majority of AIED patients to include themselves in a randomized controlled clinical trial, whose goal is to evaluate a strategy to take advantage of the potential (but not yet proven) benefits of early treatment of HIV infection while still avoiding life-long HAART. This approach will also yield generalizable data, because what is being tested is a strategy, not a specific drug regimen.

DURATION: 36 months.

SAMPLE SIZE: 180 subjects*.*

POPULATION: Patients documented to have become infected with HIV within the previous 12 months

STRATIFICATION: Acute vs. Early HIV infection (appendix V)

INTERVENTION: The only intervention will be the prescription of HAART regimens (as defined by DHHS guidelines at the time of initiation of therapy) for a period of 12 months in subjects randomized to the treatment arm of the study vs. no treatment in subjects randomized to the observational arm of the study.

## 1.0 HYPOTHESIS AND STUDY OBJECTIVES

###

### 1.1 Hypothesis

### We hypothesize that time-limited HAART (TL-HAART) given for 12 months and initiated in the first year of HIV infection will reduce the need for long-term use of HAART, and/or prolong the interval in which HAART will not be needed according to DHHS treatment guidelines for chronic HIV infection.

### 1.2 Primary Objective

To compare the steady state viral load (plasma HIV RNA concentration) in patients who have received TL-HAART to that achieved in similar patients who did not receive any antiretroviral treatment.

###

### 1.3 Secondary Objectives

1. To compare the steady state and trajectory of CD4 lymphocyte counts achieved in patients receiving TL-HAART to that achieved in similar patients who did not receive any treatment.
2. To compare the steady state and trajectory of viral load achieved in patients receiving TL-HAART in acute infection to that achieved in patients with receiving TL-HAART in early infection.
3. To compare the steady state and trajectory of CD4 lymphocyte counts achieved in patients receiving TL-HAART in acute infection to that achieved in patients with receiving TL-HAART in early infection.
4. To assess the safety and tolerability of TL-HAART in patients with acute or early HIV infection.

## 2.0 INTRODUCTION

###

### 2.1 Background

In 1996, the availability of HAART revolutionized the model of care for HIV infection. It was thought that the use of HAART could “cure” HIV infection in 3 years (2), but subsequent research has shown this model to be incorrect (3), and that long-term use of HAART is associated with significant morbidity (4). It is now felt that a well-monitored individual with chronic HIV infection and a CD4 cell count > 350 cells/mm^3^ can safely delay initiation of HAART unless plasma HIV RNA is very high (1; 5). Apart from these considerations, acute HIV infection and early HIV disease is still felt to represent a different condition from chronic HIV infection for at least three important reasons:

1) the host's immune system can be better preserved, both quantitatively and qualitatively (6)

2) the viral isolates that are transmitted may still be oligoclonal (as opposed to polyclonal in the chronic phase of the infection) and thus would be amenable to more efficient host immunologic control (7)

3) the HIV-specific immune response is still present during the first months of infection (8)

These factors, as well as some preliminary data to suggest that viral reservoirs in lymph nodes may not be fully established (9), have been presented as justification for a more aggressive therapeutic approach to acute/early HIV infection (10). Although it was initially hoped that HAART could be instituted early enough after the acquisition of HIV infection to prevent establishment of a latent viral reservoir, this reservoir appears to be established before HAART can be started (11), perhaps within 48 hours of infection (3). Current estimates are that there are about 40,000 new cases of HIV infection annually in the USA (12) and 2,100 in Canada (13). In both countries, very few cases of new infection are identified and treated in the first year of infection. A demonstration of the benefits of early treatment would be important as a means of improving the health of the infected person and as an impetus to improve methods of screening for new infections. For an individual patient treated with HAART early in HIV infection, each year of delay in the subsequent need for HAART would represent a savings of an estimated $12,000 USD drug costs and $7200 USD in other costs (14). Further, a reduction in plasma viral load set point as a result of early antiretroviral treatment could represent a major benefit with respect to secondary acquisition of HIV infection. In a recent study of HIV-infected men, multivariate analysis revealed that each log_10_ increment of plasma viral load was associated with an increase of 81% in the rate of HIV transmission from the male to the female sexual partner (15).

Smith et al (26) recently reviewed the literature on treatment of primary HIV infection. These authors, who are recognized leaders in the pathogenesis and treatment of acute and early HIV infection, concluded their review as follows:

Where does this leave the clinician who has identified a patient as acutely infected with HIV? In some regards, the question of when to treat in PHI [primary HIV infection] is similar to those patients identified with established infection; however, at the start of the disease course there is the possibility of proportionally larger benefits, making this an important question to answer. Based on the currently published data, there is no clear evidence that patients with access to antiretroviral therapy have any greater clinical benefit if therapy is introduced immediately during or prior to their seroconversion illness [67]. Despite numerous studies, none has been appropriately powered and controlled to answer this question, and we conclude that a randomized controlled trial of early short-term HAART versus deferred HAART therapy is both ethically justifiable and necessary.

It is recognized that some potential participants will have strong feelings regarding the use of HAART and may not wish to enter a protocol in which the decision to treat them will be made randomly. It is our belief that a sufficient number of people will be willing to enter a randomized trial so that our ability to accrue the desired number of participants will not be compromised.

### 2.2 Rationale

###

**2.2.1 Rationale for the strategy of not specifying HAART regimens.** The consideration of HAART in all patients with acute/early HIV infection is consistent with current DHHS guidelines for the treatment of HIV infection (16). These guidelines recommend that treatment be considered within 0-6 months of infection, but there are no data to establish either a benefit of treatment within 6 months or a lack of benefit from 6 to 12 months. At the present time, there is no consensus on the appropriate selection of initial HAART regimens for early HIV infection therefore any preferred or alternative regimen listed in the DHHS guidelines at the initiation of therapy will be allowed, and addition of a 4^th^ agent (provided not contraindicated with any of the other drugs) will also be permitted. The use of resistance testing to guide drug selection and the implementation of specific strategies to increase adherence appear to be important to ensure the success of a given regimen. When appropriate, DOT administration will be used within established programs. In all cases, selection of therapy will be optimized based on the results of genotypic resistance testing. The entry visit will take place within 14 days of screening. For those participants randomized to receive therapy, it will be started at this visit. If the results of the genotype are available at this time they will be used to determine the HAART regimen. If the results are not available treatment will be started empirically with a regimen that meets the DHHS definition of HAART which will be adjusted if necessary upon receipt of the genotype. Patients for whom no HAART regimen can be prescribed (such as would be the case for a multi-drug resistant isolate) will be excluded from the study. The use of multiple therapeutic options within each drug class is a strength of our design, allowing us to test the efficacy of a strategy (immediate vs. deferred treatment) rather than the efficacy of a single regimen. The flexibility of our design will allow us to remove HAART regimens as they are demonstrated in future clinical trials to be sub-optimal, without affecting our study design. Conversely, we will be able to add new HAART regimens as they are shown to be effective and become available in our centers. This feature may actually help us recruit patients into the trial on an ongoing basis, avoiding the problem of subjects refusing to enroll because they would not have access to a regimen they would most prefer or to the most up-to-date regimens. It will also help adherence to medications and retention of study participants.

**2.2.2 Rationale for the selection of one year as the duration for Time-Limited HAART (TL-HAART)**. TL-HAART represents a compromise to maximize the potential benefit of aggressive therapeutic intervention while minimizing the potential for a negative outcome. Most of the short-term side effects of HAART are manageable either by symptomatic treatment or drug substitution. TL-HAART avoids the long-term metabolic and morphologic toxicities of HAART. TL-HAART permits more vigorous methods (such as DOT) to maximize adherence and avoid development of drug resistance since the participants will be on therapy for only one year.. The potential benefits of the intervention (enhanced host immunity and decreased establishment of viral reservoirs and quasi-species) would all be expected to take place within the first year of therapy. The rationale for the choice of one year as the duration for TL-HAART is based on studies of the immune recovery that begins when HAART is initiated. Although circulating CD4^+^ T cell levels begin to rise very soon after this time, this is mostly due to redistribution of memory cells rather than production of new (naive) cells, which requires several months to one year to occur (24). In the MACS cohort, CD4^+^ T cell counts rose for the first two years after initiation of HAART (25). Thus, one year of therapy seems a reasonable balance between the need to suppress viremia long enough to preserve HIV-specific CD4^+^ T cells without removing the antigenic stimulus for HIV-specific CD8^+^ T cells, and allowing maximal recovery of naive CD4^+^ T cells without incurring long-term toxicities of HAART.

## 3.0 STUDY DESIGN

Within the context of a three-year randomized clinical trial, we will examine whether a one-year course of HAART provides lasting benefit in patients with acute/early HIV infection. If this is the case, we will further examine whether the benefit is limited to a subset of such individuals, based on the presumed interval between exposure to HIV and initiation of therapy. The highlights of the experimental design will be: 1) to attempt to include all patients known to have been infected within the past 12 months, with emphasis on the recruitment of patients identified prior to the development of a complete anti-HIV antibody response ("pre-seroconversion"); 2) to allow for the individualization of the treatment regimen; and 3) to administer HAART for a pre-determined length of time and then discontinue therapy.

The date of HIV infection will be estimated for all study participants according to an algorithm designed by the AIEDRP Disease Stage Working Group, which includes both [name] and [name]. Three sets of circumstances may apply:

1. There are data to support a discrete exposure to HIV accounting for transmission of HIV. In this case, the date of this exposure will be taken as the date of infection if it has occurred 4 - 42 days before the first positive HIV plasma viral load with a negative HIV antibody test, 10 - 56 days before the first indeterminate HIV antibody test, or at least 14 days before the first positive HIV antibody test.
2. There are multiple exposures to HIV and a medical history compatible with an acute retroviral syndrome. In this case, the infection date will be estimated as 14 days prior to the onset of symptoms if the symptoms started 0 - 28 days before the first positive HIV plasma viral load with a negative HIV antibody test, 3 - 35 days before the first indeterminate HIV antibody test, or at least 7 days before the first positive HIV antibody test.
3. There is no history of a specific exposure to HIV. In this case, the infection will be dated as having occurred 21 days previously (positive HIV plasma viral load with a negative HIV antibody test), 28 days previously (positive HIV plasma viral load with an indeterminate HIV antibody test) or 85 days previously (positive HIV antibody test AND a negative detuned (less sensitive) HIV antibody test).

A Western blot will be considered negative if no bands are present, and indeterminate if some bands are present but criteria for positivity are not met. If more than one set of circumstances is met, the first will be applied.

Staging of HIV infection (acute vs. early) will be determined using the AIEDRP algorithm (Appendix V)

Taken as a whole, our approach will allow for a precise classification of individuals according to the timing of infection, enhancing our ability to test the protocol’s main hypothesis in the overall study group as well as in sub-groups representing earlier infection.

Those who agree to take part in the clinical trial and meet the inclusion criteria will be randomized either to receive TL-HAART, or to be followed off therapy. After eligibility has been established, patients will be seen within 14 days (of screening) for randomization, then at weeks 1, 2, and 4 (1 month), then every month for the next 11 months over the one-year randomization period. Thereafter, follow-up will be quarterly for the duration of the study.

For those randomized to receive therapy, the specific regimen will be selected by the study physician and the participant, according to DHHS guidelines current at the time of initiation of HAART, and modified as necessary based on the results of genotypic resistance testing conducted in real time. Early on, the evolution of anti-HIV antibodies will be measured if a fully positive Western blot test was not present at baseline. On a number of occasions, more extensive blood sampling will be done, for storage of serum, plasma, and peripheral blood mononuclear cells to test additional virologic and immunologic hypotheses that will be generated in the course of this work.

In treated patients, TL- HAART will be discontinued after 12 months of therapy, unless there is a medical contraindication to doing so, such as chronic HBV infection, CD4 cell count

< 350, or pregnancy.

**The principal study endpoint will be a comparison of the plasma viral load (plasma HIV RNA concentration) 24 months after initial presentation in treated vs. untreated patients.** Additional study endpoints will be: The plasma viral load 36 months after initial presentation in treated vs. untreated patients; the CD4 lymphocyte count 24 and 36 months after initial presentation in treated vs. untreated patients; The plasma viral load and CD4 lymphocyte count 24 and 36 months after initial presentation in patients treated in the acute vs. early stage of infection (this is the parameter that was the basis for the calculations of the study’s power); the need to initiate (or re-initiate, for those who were in the treatment arm) HAART over the period of observation in all treated vs. untreated patients; toxicity of HAART in all treated patients.

Those who decline to participate in the study or do not meet the inclusion criteria will be excluded from this study and will be given referrals to local care providers with expertise in treating HIV infection.

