4.1.2 No prior antiretroviral therapy (other than post-exposure prophylaxis)

4.1.3 For subjects who have been infected with HIV-1 for more than six months at study entry: HIV-1 RNA > 5,000 copies/mL obtained within 30 days of initiation of therapy performed by any laboratory that has a CLIA certification or its equivalent.

4.1.4 Laboratory values obtained within 30 days of initiation of therapy:

- Absolute neutrophil count (ANC) ≥ 750/mm^3^.
- Hemoglobin ≥ 7.0 g/dL.
- Platelet count ≥ 50,000/mm^3^.
- Creatinine ≤ 3 x upper limit of normal (ULN).
- AST (SGOT), ALT (SGPT), and alkaline phosphatase ≤ 5 × ULN.
- Total bilirubin ≤ 2.5 x ULN.

4.1.6 Negative serum pregnancy test at screening and negative urine or serum pregnancy test at the time of initiation of therapy in women of childbearing potential.

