### 9.2 Endpoints

9.2.1 Primary Endpoints

- Comparison of the plasma viral load 24 months after initial presentation in all treated vs. untreated patients.

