9.2.2 Secondary Endpoints

- Comparison of the plasma viral load 36 months after initial presentation in all treated vs. untreated patients.
- Comparison of the CD4 lymphocyte count 24 and 36 months after initial presentation in all treated vs. untreated patients.
- Comparison of the plasma viral load 24 and 36 months after initial presentation in patients treated in the acute vs. early stage of infection.
- Comparison of the CD4 lymphocyte count 24 and 36 months after initial presentation in patients treated in the acute vs. early stage of infection.
- Toxicity of HAART in all treated patients.

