### 9.3 Randomization and Stratification

### 9.4 Sample Size and Accrual

###

Viral load set points will be evaluated at 12 and 24 months after completion of the 12 months randomization period, i.e., 24 and 36 months after entry into the study. For each patient, we observe the viral load at the pre-defined times and compare the treated and untreated groups. Based on preliminary studies at Weill Cornell School of Medicine in which the mean viral load set point after stopping HAART was 4.2 log_10_ copies/ml with SD = 0.5 log_10_ copies/mL, we anticipate a standard deviation of 0.5 log_10_ copies/mL for the plasma viral load at the times this endpoint will be measured. This is illustrated in the sample size tables below. Further, based on data from the study by Mellors et al from the MACS, which suggest that a difference of 0.25 log_10_ copies/mL may confer a meaningful long-term clinical benefit, we have evaluated our expected power to detect a difference of this magnitude. Based on these assumptions, we can calculate the number of patients/group that would be required to achieve a given power for detecting a specific measured virologic benefit of TL-HAART:

| Virologic Benefit of TL-HAART | N/group for β=0.80 | N/group for β=0.90 |
| --- | --- | --- |
| 0.25 log_10_ copies/mL | 64 (93, 144)^*^ | 84 (121,189) |
| 0.50 log_10_ copies/mL | 16 (24,36) | 21 (31,48) |
| 0.75 log_10_ copies/mL | 7 (11,16) | 10 (14,21) |

* Power assuming a standard deviation of 0.5 (0.6, 0.75) log_10_ copies/ml of HIV RNA, and α=0.05.

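### Section 3.0 names the wrong comparison as the basis for power, and the stage objectives compare treated patients only rather than the treatment effect between stages

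*Protocol*

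**What the plan says.** **Power basis.** Section 3.0 first names 24-month viral load, treated versus untreated, as the principal endpoint. It then lists additional endpoints, one of which is viral load and CD4 count at 24 and 36 months, acute-treated against early-treated patients. A parenthesis ties the power of the study to this endpoint, in the words "this is the parameter that was the basis for the calculations of the".

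Section 9.4 describes the sample size differently: "For each patient, we observe the viral load at the pre-defined times and compare the treated and untreated groups". It assumes SD 0.5 log10 (0.6 and 0.75 as alternatives), a difference of 0.25 log10 and alpha 0.05, and claims more than 90% power with 90 per group. Section 9.2.1 agrees with 9.4; its primary endpoint is "Comparison of the plasma viral load 24 months after initial presentation in all treated vs. untreated patients".

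**Stage question.** The Schema and section 3.0 ask whether the benefit of one year of HAART is confined to some patients according to time since infection. Objective 2 in section 1.3 is worded as "To compare the steady state and trajectory of viral load achieved in patients receiving TL-HAART in acute infection to that achieved" in treated early infection, and objective 3 does the same for CD4 count. Section 9.2.2 carries this into two endpoints, the first being "Comparison of the plasma viral load 24 and 36 months after initial presentation in patients treated in the acute vs. early stage of infection"; the second is the CD4 counterpart. The Schema makes stage a stratification factor.

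**Analysis.** Section 9.6 plans treatment-group comparisons within each stage, and a further regression with baseline viral load and CD4 count, stage, treatment and their interaction. Section 9.0 allows the unpaired t-test and repeated-measures ANOVA for comparisons between sub-groups.

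**Entry rule.** Criteria 4.1.3 and 4.2.3 set a viral-load floor of 5,000 copies/mL only "For subjects who have been infected with HIV-1 for more than six months at study entry". Appendix V classes 6 to 12 months after seroconversion as early.

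**The concern.** There are two separate problems.

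First, section 3.0 and section 9.4 disagree on which comparison the trial was sized for. Anyone who relies on 3.0 would believe that a secondary contrast within one arm has the power that 9.4 gives to the randomized comparison. It does not.

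Second, comparing acute-treated with early-treated patients does not answer the question the protocol asks. Benefit means treated against untreated, so asking whether benefit depends on stage is asking about a difference between two treatment effects. Patients are not randomized to a stage. A lower 24-month viral load in acute-treated than in early-treated patients could arise from natural differences between the stages, even if TL-HAART had no effect in either. The entry floor acts in the same contrast: it removes low viral loads from part of the early stratum and, in practice, none of the acute stratum, which tilts the comparison in favour of treating acutely.

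**Working it through.** **Inputs.** From section 9.4: difference 0.25 log10; SD 0.5, 0.6 or 0.75; alpha 0.05 (sidedness not stated; two-sided reproduces the plan's sample sizes closely); 90 per group; 60 acute subjects (30 per arm) and 120 early (60 per arm). No dropout allowance is made there, and none is made here unless stated.

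**1. The plan's own figure.** Power = Φ(δ/SE − 1.96), with SE = SD × √(1/n₁ + 1/n₂).
- Treated vs untreated, 90 vs 90, SD 0.5: SE = 0.5 × √(2/90) = 0.0745; 0.25/0.0745 = 3.354; Φ(1.394) = 91.8%. The claim of more than 90% reproduces.
- N per group at 0.25 log10 for 80% power: computed 63 (91, 142) against the printed 64 (93, 144). For 90%: computed 85 (122, 190) against 84 (121, 189).

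So 9.4 is a calculation for treated versus untreated.

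**2. The contrast named in section 3.0.** Acute-treated 30 vs early-treated 60: √(1/30 + 1/60) = √0.05 = 0.2236.

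| SD | SE | 0.25/SE | Power |
|---|---|---|---|
| 0.5 | 0.1118 | 2.236 | 60.9% |
| 0.6 | 0.1342 | 1.863 | 46.2% |
| 0.75 | 0.1677 | 1.491 | 31.9% |

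At SD 0.5, an assumed loss of 10% or 20% lowers 60.9% to 56.4% or 51.6%. Reaching 80% at SD 0.5 would need 48 acute-treated and 96 early-treated patients, or 2 × 144 = 288 randomized in the same mix.

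This 61% is not the 61% (46, 32) printed in the second table of 9.4. That entry is labelled as the treatment benefit in subjects infected 2 to 12 months. The figures agree because 1/30 + 1/60 = 2/40, so 30 vs 60 has the precision of 40 per group, and the printed column reproduces at 40 per group rather than at its labelled 60 (which gives 78%). That labelling problem is a separate matter.

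**3. The contrast that answers the stage question.** Difference in treatment effect between strata, 30/30 and 60/60: SE = SD × √(2/30 + 2/60) = SD × √0.1 = SD × 0.3162. The difference detectable with 80% power is (1.960 + 0.842) × SE.

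| SD | SE | 80% power needs |
|---|---|---|
| 0.5 | 0.158 | 0.44 log10 |
| 0.6 | 0.190 | 0.53 log10 |
| 0.75 | 0.237 | 0.66 log10 |

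These figures ignore dropout (which would raise them) and baseline adjustment (which could lower them).

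**4. The entry floor.** Its effect at 24 months cannot be derived from the protocol. It would need the entry viral-load distribution, the share of early subjects infected more than six months, and the correlation between entry and month 24. Purely as an illustration, assume entry values are normal with mean 4.2 and SD 0.5. The floor at log10(5,000) = 3.70 then excludes about 16% of those it applies to and raises their entry mean by about 0.14. With an assumed 25% to 100% of the early stratum under the floor and a correlation of 0.3 to 0.7, the shift in the early mean at 24 months runs from 0.14 × 0.25 × 0.3 ≈ 0.01 to 0.14 × 1 × 0.7 ≈ 0.10 log10.

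**The case against.** The strongest reply is that the remark in 3.0 is a misplaced parenthesis, or refers loosely to viral load as the measured quantity. The emphasized sentence earlier in the same section, 9.2.1 and 9.4 all make treated versus untreated the principal comparison, and its power claim reproduces. This is very likely right about the cause. The text still attaches the power basis to the wrong contrast. A reader might go on to infer that the trial was underpowered for its primary endpoint; the protocol does not support that, since the 61% belongs to a secondary contrast that it never sized.

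On the stage question, 9.6 already does much of what is needed. It compares randomized groups within each stage, prespecifies the interaction for each endpoint, and warns against reading a difference from separate subgroup results. These analyses would expose a stage difference that had nothing to do with treatment. That stands, and it limits the harm. What remains is that the objectives and endpoints define a contrast that 9.6 never names, while 9.0 leaves it open to an unadjusted t-test.

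On the entry floor, it is tempting to set the 0.14 log10 beside the 0.25 target and call it more than half the effect. The documents do not support that. The 0.14 is an entry-level shift in only part of the early stratum, and its mean and SD are those 9.4 gives for set points after stopping HAART. The baseline adjustment in 9.6 would reduce the selection. The floor also applies to both arms, so it does not bias the randomized comparison.

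Finally, the protocol claims no power for the interaction, and 0.25 log10 is its target for the treatment benefit, not for a difference in benefit. The limited precision of the interaction therefore contradicts nothing; it should simply be stated.

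**Conclusion.** The point holds on two counts. Section 3.0 is wrong as written about the basis for power: 9.4 sizes treated versus untreated, and the contrast 3.0 names would have about 61%, 46% or 32% power for 0.25 log10 at SD 0.5, 0.6 or 0.75, with 30 vs 60 patients and no dropout. Objectives 2 and 3 and the two stage endpoints in 9.2.2 rest on a non-randomized, treated-only contrast that cannot separate a TL-HAART effect from differences between stages. The one-sided entry floor adds selection to that contrast. Its direction is clear, but its size at 24 months is not derivable.

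The primary endpoint, its randomized comparison and the planned 180 subjects are not called into question here. This is an error of statement and alignment that should be corrected, not a flaw in the main design.

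**What to change.** 1. In section 3.0, move the parenthesis on power to the principal endpoint, treated versus untreated viral load at 24 months.
2. In sections 1.3 (objectives 2 and 3), 3.0 and 9.2.2 (the two stage endpoints), define the quantity of interest as the difference between strata in the TL-HAART effect, treated minus untreated. Name the stage-by-treatment interaction in 9.6 as its test, and report the estimate with a confidence interval.
3. Keep acute-treated versus early-treated as a descriptive summary, noting that it is not randomized and that the viral-load floor applied to part of the early stratum only.
4. State the precision of the interaction: 80% power for a difference in effect of about 0.44, 0.53 or 0.66 log10 at SD 0.5, 0.6 or 0.75, before dropout and baseline adjustment.

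The cost is wording in a few sections. The analysis is already planned, and no further subjects, visits or data are needed. The drawback is that the stated precision for the stage question becomes less favourable.
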